### **Follow-up visit**

Follow-up visits will take place approximately every six months (more or less 2 months). They will make it possible to follow the progression of the treatment and the evolution of the quality of life. The following actions will be performed at each follow-up visit:

- A pair of low-dose EOS digital x-rays will be acquired: simultaneous AP and lateral while the patient is standing in a comfortable position, with hips and knees extended, hands lateral to the head.
- The SRS-22r questionnaire will be administered.

If necessary, a renewal of brace can be prescribed, according to the judgment of the orthopedist and the orthotist. If the brace needs to be renewed, the following additional interventions will be performed:

- A scan of the external surface of the trunk will be acquired with the TechMed3D surface scanner.

### **Brace renewals**

If a brace renewal is prescribed, the new brace will be designed according to the initial design method (control or test) detailed in section 5. The brace will be returned to the clinic approximately one month later, following the usual procedure. During the brace delivery, the following actions will be performed:

- Minor adjustments to cutouts and topology to ensure patient comfort following the same procedure as original delivery
- Installation of an iButton to monitor wearing time
- A digital x-ray will be acquired in a supine position with the patient in a comfortable position, with hips and knees extended, hands in a lateral position relative to the head.

### **6.5. Failure criteria**

The failure criteria for the treatments are those mentioned in secondary hypothesis H2.

Note that a patient in phase #1 is likely to have immediate failure of the brace assigned to them for phase #2. In this case, for ethical reasons, the brace of the other group will be assigned to him. Also for ethical reasons, a patient may have to use the brace of the other group during phase #2 if it offers an immediate correction of the Cobb angle greater than 5 degrees.

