## 4. Objective and assumptions

**The general objective** of the project is to validate the new CAD/CAM brace design method integrating the optimization of immediate correction.

**Primary Hypothesis (H1)** : After 1 year and 2 years of use, the out-of-brace correction, as measured by Cobb's angle, from the Test braces will be non-inferior to the Control braces. The non-inferiority margin will be 5 degrees.

**Secondary hypothesis (H2)** : The immediate and medium-term (1 and 2 years) failure rate of treatment will be 10% lower for Test braces compared to Control braces. There are three different types of failures:

1. Mid-term failure (1 and 2 years) – relative progression : A progression of the out-of-brace Cobb angle of 5 degrees or greater than the value measured at visit 1.
2. Intermediate (study duration) failure – absolute progression : A progression of the Cobb angle of the main off-brace curvature to greater than 45 degrees (SRS failure criterion).
3. Medium-term failure (duration of the study) – surgery : Stopping treatment with a brace and a decision to have surgery (AVBGT or fusion).

**Secondary hypothesis (H3)** : The quality of life of patients wearing Test braces in the medium term, as measured with the SRS-22r questionnaire, will be non-inferior to that of patients wearing control braces. The non-inferiority margin will be 10%.

**Secondary hypothesis (H4)** : The immediate in-brace correction of the Cobb angle of the Test brace will be no less than that of the control brace. The non-inferiority margin will be 5 degrees.

The effects measured (dependent variables) are as follows:

| Effects measures                                                         | Descriptions                                                                           |
|--------------------------------------------------------------------------|----------------------------------------------------------------------------------------|
| Major                                                             |                                                                                        |
| Cobb angle off brace (Initial, 6 months, 1 year, 2 years).               | Measure using low-dose EOS radiography to assess the evolution of scoliosis.           |
| Secondary                                                         |                                                                                        |

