### Proof of concept and preliminary results

The process for generating optimized braces was tested numerically on eight cases by comparing their correction efficiency with that of reference braces. The design time required was five minutes for the semi-automatic process and approximately 1h30 for the reference brace. For these preliminary results, the immediate lumbar correction was significantly better (55% vs 31%,  $p = 0.004$ ) for an equivalent level of pressure exerted on the trunk.

The immediate correction simulation method has already been carried out by our group. It had been shown that the position lying on the back made it possible in part to correct the deformation of the column and that the Providence-type brace came to rebalance the forces on the growth plates of the vertebrae.

The brace will be adapted to include a compliance monitor. This will in no way affect the correcting effect of the brace. The compliance monitor is an iButton thermal sensor ( *Boston Brace, MA, USA* ), this will record the wearing time of the brace. The new type of brace (test brace) will be manufactured in the same way by CAM and thermoforming in the facilities of Orthèse-Prothèse Rive-Sud .

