## **7. Randomization**

Patients who meet all the inclusion criteria and no exclusion criteria will be randomized twice independently.

Randomization #1 will be to determine the trial sequence of brace types at Visit #2. Randomization #1 allocation will have a 1:1 ratio for the “test:control” sequence and the “control” sequence. : test ”.

Randomization #2 will be to determine the brace type the patient will use for a period of two years after the visit. The allocation will have a ratio of 1:1 for test and control brace type respectively.

The randomization will be done by the URCO nurse coordinator according to a block allocation of 2, 4 or 6. Neither the engineers nor the orthopedist nor the orthotist will know the brace assigned for phase #2 until these are designed, manufactured and adjusted.

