## 8. Statistical analysis plan

### 8.1. Sample size justification

The sample size was calculated to be able to accept the main hypothesis (H1) with a probability of 5% of committing the type I error and a power of 80%. The calculation was performed with nQuery software (GraphPad Software DBA Statistical Solution, San Diego, CA) and the following parameters were used:

- Significance level  $\alpha = 5\%$
- Allocation ratio  $k = 1$
- Margin of non-inferiority  $\delta = 5^\circ$
- standard deviation  $\sigma = 7^\circ$ 
- Power  $(1 - \beta) = 80\%$

The sample size should be 25 per group, so a total of 50 patients. On the other hand, a loss to follow-up of 15% is anticipated. We will therefore need 29 patients per group for a total of 58 patients.

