### 8.2. Types of analyzes

There will be two types of data analysis: an intention-to-treat (ITT) analysis and a per-protocol (PP) analysis. Data analysis by ITT will include all patients who have been randomized. A study on patient compliance shows that, on average, patients wear the night brace 90.7% of the prescribed time (generally 8 hours). For this reason there will also be an analysis of the results by PP which will only include patients who have worn the brace on average for more than 7.2 hours per day. This method of analysis will make it possible to evaluate the correction of the brace if it is worn with good compliance.

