### 8.3. Analysis of primary hypothesis H1

The analysis of primary hypothesis H1 will have the off-brace Cobb angle as the dependent variable and the type of brace worn as the independent variable. The 95% confidence interval of the difference in correction between the test brace and the control brace will be constructed and compared to the non-inferiority margin.

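### Patients can be moved to the other arm's brace on their Visit 2 result, but H1 to H3 compare by brace worn and the per-protocol set filters only on hours, so neither stated analysis handles the switches

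*Protocol*

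**What the plan says.** - **Allocation (section 7).** Randomization #2 fixes the brace for two years: "The allocation will have a ratio of 1:1 for test and control brace type respectively".
- **Switching (section 6.5).** There are two routes out of the allocated arm. After an immediate failure in phase 1 the patient is given the other group's brace. Separately, "a patient may have to use the brace of the other group during phase #2" if that brace gives an immediate Cobb correction above 5 degrees.
- **Analysis sets (section 8.2).** For intention to treat, "Data analysis by ITT will include all patients who have been randomized"; the grouping of those patients is not stated. The per-protocol analysis will "only include patients who have worn the brace on average for more than 7.2 hours per day". Switching is not mentioned.
- **Comparison (sections 8.3 to 8.5).** H1, H2 and H3 each take "the type of brace worn as the independent variable".
- **Margin (section 4, H1).** "The non-inferiority margin will be 5 degrees".

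**The concern.** The two routes in section 6.5 depend on the in-brace result at Visit 2, which is seen after enrolment and allocation. Section 3.3 reports a strong correlation between immediate Cobb correction and correction of growth-plate pressure asymmetry, and presents it as the biomechanical link to long-term effect. The switching variable is therefore plausibly prognostic.

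Each reading of the plan has a weakness:

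- **As worn** (the text of sections 8.3 to 8.5): patients who do badly in one brace are moved into the other group, so the groups are no longer those formed by randomisation.
- **As randomised** (the usual meaning of ITT): switched patients carry the other brace's effect, and the observed difference shrinks towards zero. In a superiority trial that is conservative. Here it makes an inferior brace easier to declare non-inferior.
- **Per protocol**: a switched patient who wears the other arm's brace for 8 hours a night passes the 7.2-hour filter and stays in.

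At stake is the primary conclusion that the test brace is not worse by 5 degrees or more.

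**Working it through.** **The plan's own figure.** Section 8.1 sizes the trial "with a probability of 5% of committing the type I error and a power of 80" per cent, with margin 5, SD 7 and 1:1 allocation. n per group = 2 × (7/5)² × (z₁₋α + 0.842)².
- One-sided 5%: 2 × 1.96 × (1.645 + 0.842)² = 24.2, so 25. This reproduces the protocol; the exact t calculation also gives 25 (power 80.1%).
- One-sided 2.5%: 2 × 1.96 × (1.960 + 0.842)² = 30.8, so 31 (exact t: 32). This does not match.

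The sample size is not in dispute, but it has no allowance for switching. The two-sided 95% interval in section 8.3 implies a nominal false non-inferiority rate of 2.5%, which is the baseline below.

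**Assumptions that the protocol does not supply.** D is the within-patient difference between the two Visit 2 in-brace Cobb angles, normal with mean 0 and SD 5 or 7. I read the 5-degree rule as the other brace correcting by more than 5 degrees more than the assigned one. The true follow-up inferiority of the test brace is 5 degrees, with 25 per group and outcome SD 7. Only the 5-degree rule is modelled, because immediate failure is undefined.

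**Eligible to switch, per arm.** P(D > 5) = 1 − Φ(5/SD): 1 − Φ(1.00) = 15.9% at SD 5; 1 − Φ(0.714) = 23.8% at SD 7.

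**As randomised, closed form.** Observed difference = 5 × (1 − sum of the two switch fractions). SE = 7 × √(2/25) = 1.98. Error ≈ Φ(5 × sum / 1.98 − 1.96).
- SD 5, all switch: sum 0.317, difference 3.41, Φ(0.80 − 1.96) ≈ 12%.
- SD 7, all switch: sum 0.475, difference 2.63, Φ(1.20 − 1.96) ≈ 22%.

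**Simulation of the same set-up** (false non-inferiority, nominal 2.5%; repeat runs differ by about one percentage point):

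| Analysis | SD 5 | SD 7 |
|---|---|---|
| ITT as randomised, all eligible switch | 11–12% | 20–21% |
| ITT, half switch | 6% | 8% |
| ITT, a quarter switch | 4% | 5% |
| As worn, all switch, half of D persists to follow-up | 8–9% | 17–18% |
| As worn, all switch, none of D persists | about 2.5% | about 2.5% |
| Dropping actual switchers only, half of D persists | 5% | 8–9% |
| Dropping both arms' patients with a difference above 5 degrees | about 2.5% | about 2.5% |

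At the one-sided 5% level that section 8.1 appears to use, ITT error at SD 5 with full switching is about 19%.

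**Size of the symmetric set.** P(|D| ≤ 5) is 68% at SD 5 and 52% at SD 7, that is about 17 and 13 per arm. Power with a 95% interval is then about 52% and 42%.

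**Size of a per-protocol set without switchers, before the hours filter.** 25 × (1 − 0.159) ≈ 21 or 25 × (1 − 0.238) ≈ 19 per arm. Power ≈ Φ(5 / (7√(2/n)) − 1.96): Φ(0.36) = 64% or Φ(0.24) = 60%, against Φ(0.57) = 71% at 25 per arm.

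**The case against.** **ITT is named, and the wording may be loose.** Section 8.2 does promise an analysis of all randomised patients, and the phrase in sections 8.3 to 8.5 may simply mean the treatment factor. That is possible, and finer handling of switchers is often left to a separate analysis plan. But section 8 states both the grouping variable and the per-protocol rule. These are choices that conflict, not omissions, and a true as-randomised ITT is still diluted.

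**ITT can be read as comparing policies.** Starting in one brace and swapping if the other is better is a legitimate policy, and for it the diluted difference is the right answer. H1, however, is worded about the braces themselves.

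**The inflation depends on uptake.** The 5-degree rule is permissive, no rate is given, and at a quarter uptake the ITT error is only 4 to 5%. As-worn grouping holds its level if the immediate difference does not predict outcome. Both points stand, so the size can only be given as a range.

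**A stronger reading is tempting.** A reader might take the 55% against 31% lumbar correction in section 5.2 to mean that most control patients would switch and little randomised contrast would remain. The documents do not support this. The figure comes from eight numerically tested cases and concerns lumbar correction only, and section 9.1 says the optimised brace's effectiveness is unknown. Error rates built on it also pair a large immediate gain with worse follow-up, which sits badly with the link drawn in section 3.3.

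**Conclusion.** The point holds and should be settled before analysis. The grouping variable for H1 to H3 contradicts the ITT analysis, and no stated analysis guards against planned switching. That part rests on the text alone.

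The size rests on the assumptions listed: no mean immediate difference, within-patient SD 5 to 7 degrees, 25 per group, outcome SD 7, true inferiority 5 degrees and a two-sided 95% interval. Against a nominal 2.5%, ITT error is about 11 to 20% with full switching, 6 to 8% with half and 4 to 5% with a quarter. As-worn error with full switching is about 8 to 17% if half of the immediate difference persists, and about 2.5% if none does.

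It would go too far to say that the randomised contrast is mostly lost, or that success in the symmetric set must be a condition for H1. That set is small and describes only patients with similar immediate correction in both braces. Its 2.5% level was shown for a mean difference of 0 only.

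**What to change.** 1. **Sections 8.3 to 8.5:** for ITT, replace "the type of brace worn as the independent variable" by the brace type assigned by Randomization #2.
2. **Section 8.2:** add to the per-protocol definition that patients who did not use their randomised brace, under either route in section 6.5, are excluded.
3. **Sensitivity analysis:** drop, in both arms alike, every patient whose two Visit 2 in-brace Cobb angles differ by more than 5 degrees. Dropping only actual switchers is lopsided and leaves an error of about 5 to 8% or slightly more if half of the difference persists. Report this analysis as supportive, not as a required criterion.
4. **H1:** claim non-inferiority only if ITT and per protocol agree.
5. **Reporting:** tabulate switches by arm, direction and reason.
6. **Reconcile section 6.5 with H2 in section 4.** Section 6.5 refers to H2 for the failure criteria, but the three listed there are mid-term or study-duration failures. The immediate failure that triggers the first route is therefore undefined. I take no view on the clinical rule itself.

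**Cost.** No new data are needed, but this is more than a wording change. The per-protocol set shrinks and its interval widens. The symmetric set keeps about 52 to 68% of patients if the braces are equal on average, and fewer otherwise. The power of the joint claim falls below the stated 80%, and the protocol should say so.

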## **7. Randomization**

Patients who meet all the inclusion criteria and no exclusion criteria will be randomized twice independently.

Randomization #1 will be to determine the trial sequence of brace types at Visit #2. Randomization #1 allocation will have a 1:1 ratio for the “test:control” sequence and the “control” sequence. : test ”.

Randomization #2 will be to determine the brace type the patient will use for a period of two years after the visit. The allocation will have a ratio of 1:1 for test and control brace type respectively.

The randomization will be done by the URCO nurse coordinator according to a block allocation of 2, 4 or 6. Neither the engineers nor the orthopedist nor the orthotist will know the brace assigned for phase #2 until these are designed, manufactured and adjusted.

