### **Design and manufacture of braces**

Before the second visit, which will take place approximately one month after the first, each patient will have a control brace and a test brace designed and manufactured according to the specific geometry of their trunk and spine as described in Section 5.

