#### 9.1. Risks

Patients participating in this study will receive one more digital X-ray than patients receiving conventional treatment. The risk remains low since the other x-rays are based on the EOS dose. They have up to 8-10 times less radiation than a standard X-ray. The additional X-ray seems to us to be justified given the low radiation associated with the other X-rays, because it makes it possible to compare the immediate effectiveness of the two types of braces and to ensure that a patient is not randomized in an inferior treatment.

Participants will be dressed in light, tight-fitting clothing, which could be inconvenient for some.

There is also the risk that the optimized brace will be less effective or less comfortable. The effectiveness of the optimized brace is unknown.

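### Section 7 lets the phase 2 allocation become known before the Visit 2 films decide whether it is overridden under 6.5, which leaves room for selective switching

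*Protocol*

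**What the plan says.** **Drawing the allocation.** Section 7: "Patients who meet all the inclusion criteria and no exclusion criteria will be randomized twice independently". No later time is given for Randomization #2. "The randomization will be done by the URCO nurse coordinator according to a block allocation of 2, 4 or 6".

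**End of concealment.** Section 7: "Neither the engineers nor the orthopedist nor the orthotist will know the brace assigned for phase #2 until these are designed, manufactured and adjusted". The in-brace films are not named as a condition.

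**Braces.** Section 6.4, before Visit 2: "each patient will have a control brace and a test brace designed and manufactured". Both braces exist for every patient whatever the allocation.

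**Visit 2 (section 6.4).** The text lists the orthotist's check of supports, shape and strap tension, then the supine in-brace film, then hand-over of the allocated brace unless a failure criterion is met. The Cobb angle is read by an evaluator blind to the study aims.

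**Override (section 6.5).** The section warns that "a patient in phase #1 is likely to have immediate failure of the brace assigned to them for phase #2", and continues: "In this case, for ethical reasons, the brace of the other group will be assigned to him". It adds a second route: "a patient may have to use the brace of the other group during phase #2 if it offers an immediate correction of the Cobb angle" by more than 5 degrees.

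**Rationale for the extra film (section 9.1).** It is there "to ensure that a patient is not randomized in an inferior treatment".

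**The concern.** Concealment should last until the last decision that could depend on the allocation. Here that decision is whether the patient keeps the allocated brace. The wording of section 7 lets concealment end one step earlier, at adjustment.

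The decision also leaves room for judgment. The 5-degree route is worded as a possibility. The immediate-failure route is worded as mandatory, but section 6.5 takes its criteria from H2, and none of the three failure types listed there is an immediate one. Section 6.5 does not say who decides, or that the person must not know the allocation.

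If those who decide know the allocation, they can switch more readily in one direction than in the other, and the two arms are then no longer treated alike. The planned analyses would not remove this. Section 8.3 analyses H1 by the brace worn, the intention-to-treat set contains all randomised patients, and the per-protocol set is defined by wear time only.

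**Working it through.** The plan gives no switching rate or other figure on this point, so the check is mainly of the order of events.

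**1. Does the allocation exist before Visit 2?** The date of Randomization #2 is not stated. Two passages imply an early draw. Section 7 conceals the allocation during design and manufacture, which section 6.4 places before Visit 2. Section 6.5 describes a patient still in phase 1 who already has a brace assigned for phase 2. This is a strong inference, not a stated fact.

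**2. Can it be known before the films can be compared?** The Visit 2 text can be read in two ways:

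| Reading | Order | Both braces adjusted before the last film? |
|---|---|---|
| A | adjust 1, adjust 2, film 1, film 2 | Yes |
| B | adjust 1, film 1, adjust 2, film 2 | Yes |

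Under either reading, the section 7 condition is met before both films are available, and so before any 6.5 decision that compares them.

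**3. Do other safeguards close the gap?** There are three: a reader blind to the study aims, a numeric threshold on one trigger, and a bar on modifying the corrective effect of the test brace. None of them masks the person who decides the switch.

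**4. How many patients might face the decision?** This shows exposure, not bias.

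- From the document: 58 patients and SD 7 degrees (section 8.1, where the SD serves the off-brace calculation), a 5-degree threshold (6.5), and 1:1 allocation (7).
- Assumed: the same SD applies in-brace, the braces are equal on average, differences are normal, the trigger is a between-brace difference above 5 degrees, and the within-patient correlation rho is 0.5 to 0.9.

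Let D be the test minus control in-brace Cobb angle. Its SD is s = 7 × √(2(1 − rho)). The share of discordant patients is P(|D| > 5) = 2 × [1 − Φ(5/s)]. Half of these are allocated to the worse brace.

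| rho | s (degrees) | P(\|D\| > 5) | Allocated to the worse brace, of 58 |
|---|---|---|---|
| 0.5 | 7.00 | 0.475 | 58 × 0.475 / 2 = 13.8 |
| 0.7 | 5.42 | 0.356 | 58 × 0.356 / 2 = 10.3 |
| 0.9 | 3.13 | 0.110 | 58 × 0.110 / 2 = 3.2 |

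**5. What can be recovered afterwards?** Every patient is filmed in both braces, so differences above 5 degrees can be found in both arms. The permissive and immediate-failure decisions cannot be recovered in this way. They are taken relative to the allocated brace, so nothing shows what would have been decided under the opposite allocation.

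**The case against.** The strongest reply is that section 7 sets a minimum period of concealment and does not say that the allocation is disclosed at adjustment. Visit 2 ends with hand-over, so the allocation may in practice be opened only after the films, and the word for adjustment may have been meant to include them. That is possible. But nothing in the text requires it, and one clause would settle it.

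It can also be said that one trigger is mandatory, the other has a numeric threshold, and no passage names the orthopedist or orthotist as the person who decides. This is correct, and it limits the point to an opportunity for selective switching.

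Four stronger readings are tempting, and the document does not support them:

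- **A shift in favour of the test brace.** Under the assumptions above, switching only away from the test brace would move the in-brace mean by s × φ(5/s) = 2.16, 1.41 or 0.35 degrees for rho 0.5, 0.7 or 0.9. But this is a parallel-arm in-brace contrast, which no planned analysis uses. H4 is answered by the paired phase 1 films, before any switch, and H1 is off-brace. Even-handed switching between equal braces gives no net shift, and nothing in the document indicates one-sided switching.
- **No sensitivity analysis is possible.** The paired films allow one on the numeric trigger.
- **Section 9.1 contradicts sections 6.5 and 7.** Its wording is loose and can be read as describing the 6.5 reassignment. It fixes no order of randomisation.
- **Switching as such dilutes the comparison.** It would do so under perfect concealment too, and would still do so after the change proposed here. That is a separate matter.

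**Conclusion.** The point holds in limited form. As sections 6.4, 6.5 and 7 are written, the phase 2 allocation can be known before the decision to override it, and that decision is partly permissive, partly based on an undefined criterion, and not assigned to a masked person. This weakens the double-blind label and should be corrected, but it does not show that H1 is biased.

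The conclusion rests on the inferred early draw of Randomization #2 and on the stated order of adjustment before films. About 3 to 14 of 58 patients might face the 5-degree decision under the stated assumptions. The correlation is not in the document, and neither the size nor the direction of an effect on the off-brace Cobb angle can be derived from it.

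**What to change.** - **Section 7.** Replace the condition that ends concealment with: *until both in-brace films have been read and the 6.5 decision recorded*. Draw or open Randomization #2 only then.
- **Visit 2.** Code the two films A and B for the reader. Before the allocation is revealed, record the 6.5 decision for every patient: none, or which coded brace is affected. Name who decides.
- **Analysis.** Keep this record as a pre-allocation variable, so that a sensitivity analysis can exclude flagged patients from both arms alike, including those flagged on judgment.
- **Consistency.** Reconcile 6.4, 6.5, 7 and 9.1 with this order, and reconcile the immediate-failure wording of 6.5 with the H2 list. The clinical switching rule is not changed here.

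The cost is protocol wording and a line on the Visit 2 form. Coordinator, allocation list, braces, films and evaluator stay the same. The one small downside is that both films must be read before the brace is handed over, which the failure check at delivery already implies.
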